#### Statistical power

By sampling 38 clusters (19 clusters in the intervention arm and control arm respectively) with an average of three employees in each cluster, the study population is estimated to be a total of 114, with 57 employees in the intervention group and the control group respectively. With these numbers it will be possible to achieve about 80% power to detect a difference of 30% in number of days of sick leave during the 12-month follow-up, assuming that the mean number of days in the control group is 108 [14]. The standard deviation of sick leave days was 60 days [10]. The intra-cluster correlation was set to 0.015 and a significance level of 0.05, two-sided test.

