## Background

Common mental disorders (CMD), i.e. depression, anxiety, adjustment disorders and stress-related mental disorders, are highly prevalent in the working population and have been estimated to affect about 1 in 5 persons in countries belonging to the Organisation for Economic Co-operation and Development (OECD) [1, 2]. CMDs have major consequences, affecting individuals and the society at large [3]. CMDs cause individual suffering and pose a risk of social isolation, stigmatization, and long-term sick leave [4]. In the European Union, the estimated annual costs related to mental ill-health were more than 600 billion Euros in 2015, including costs for health care systems, social security programs and indirect costs (i.e. sick leave and impaired work performance) [2].

For employees in general, and specifically for those suffering from CMDs, having paid employment is beneficial for their health [5–8]. Modini et al. identify several individual benefits of employment compared to unemployment. These include increased sense of autonomy, improved self-reported well-being, reduced depression and anxiety symptoms, increased ability to cope with demands, enhanced social status, and unique opportunities for personal development and mental health promotion [5]. The vast majority of individuals with CMDs is employed and about 30% of these employees have a first period of sick leave due to CMDs during adulthood. Around 20–30% of the 30% of employees with a first sick leave spell have recurrent sick leave episodes [9]. Hence, the total burden of sick leave (e.g. individual suffering, isolation, economic loss and societal costs) and the individual benefits of employment emphasize the importance of sick leave prevention.

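### The stated 80% power rests on a mean of 108 and an SD of 60 days, which together require at least 76% of control employees to take CMD sick leave within 12 months, a share the protocol does not justify

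*Protocol article*

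**What the plan says.** The protocol article, under Statistical power, plans 38 managers (19 per arm) with three employees each, so 57 employees per arm. It claims "about 80% power to detect a difference of 30% in number of days of sick leave during the 12-month follow-up". The planning values are "the mean number of days in the control group is 108 [14]. The standard deviation of sick leave days was 60 days": the mean is cited to reference 14 and the SD to reference 10. It adds that "The intra-cluster correlation was set to 0.015 and a significance level of 0.05, two-sided test".

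Three other places bear on these values:

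- **Primary outcome:** the total of CMD sick-leave days over 12 months for each participant, so an employee without such leave counts as zero.
- **Exclusion criteria for employees:** anyone currently on full- or part-time sick leave, and anyone with 14 or more CMD days in the preceding three months, is left out.
- **Background:** among employed people with CMD, "about 30% of these employees have a first period of sick leave due to CMDs during adulthood".

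The power paragraph mentions neither zeros nor skewness.

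**The concern.** In a prevention trial among people who are at work, a sizeable group may have no CMD sick leave in the year. A block of zeros raises the SD relative to the mean. The planning SD is only 60/108 = 0.56 of the mean, which leaves little room for zeros. Because the two values come from different studies, nothing shows that they were ever observed together in one population.

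This paragraph is the only justification of the sample size and concerns the primary outcome. If the true SD is close to the mean or larger, the trial has far less than 80% power, and a null result could be misread as evidence that the intervention does not work.

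**Working it through.** **1. The plan's own figure.** Inputs from Statistical power: 57 per arm, cluster size 3, ICC 0.015, control mean 108, SD 60, 30% reduction, two-sided 5%.

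- Design effect = 1 + (3 − 1) × 0.015 = 1.03
- Difference = 0.30 × 108 = 32.4 days
- Standard error = 60 × √(2 × 1.03 / 57) = 11.41
- 32.4 / 11.41 = 2.84; power = Φ(2.84 − 1.96) = 81% (79% by t with 36 df)

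The stated figure reproduces.

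**2. What mean 108 and SD 60 imply.** Let p be the share of controls with any CMD days. For a non-negative count, the Cauchy–Schwarz inequality gives mean² ≤ p × (mean² + SD²), so

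p ≥ 108² / (108² + 60²) = 11664 / 15264 = 0.764.

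The minimum is reached only if every leave-taker has the same total, 108 / 0.764 ≈ 141 days. Any spread among takers pushes the required share higher. Short spells cannot satisfy the bound either. The one-sided Chebyshev form requires at least 94² / (94² + 60²) = 71% of controls to exceed 14 days and at least 80² / (80² + 60²) = 64% to exceed 28 days.

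**3. Power if the share is lower.** The protocol gives no 12-month share, so p is an assumption here. Let c be the SD divided by the mean among leave-takers, also an assumption, with 0 and 1 as ends. Then

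(overall SD / overall mean)² = (1 + c²)/p − 1.

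For a 30% relative reduction, power depends only on p, c and the way the effect arises, so the same figures hold whether 108 is the mean of all controls or of leave-takers only. Three mechanisms are considered:

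- equal SD in both arms;
- spells 30% shorter, so the intervention SD is 0.7 of the control SD;
- 30% fewer takers, with durations unchanged.

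Worked case, p = 0.50, c = 0, mean 108 (takers have 216 days each, control SD 108):

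- Equal SD: SE = √((108² + 108²) × 1.03/57) = 20.53; 32.4/20.53 = 1.58; power 35%
- Shorter spells: intervention SD 75.6; SE = 17.72; 32.4/17.72 = 1.83; power 45%
- Fewer takers: intervention variance = 0.35 × 216² − 75.6² = 10614, SD 103.0; SE = 20.06; power 37%

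| p | c | Equal SD | Shorter spells | Fewer takers |
|---|---|---|---|---|
| 0.30 | 0 | 18% | 22% | 19% |
| 0.30 | 1 | 10% | 12% | 11% |
| 0.50 | 0 | 35% | 45% | 37% |
| 0.50 | 1 | 15% | 18% | 16% |
| 0.70 | 0 | 67% | 80% | 63% |
| 0.70 | 1 | 21% | 27% | 23% |

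Keeping the mean at 108 with p = 0.30 would require 108/0.30 = 360 days per leave-taker, almost the whole year. If instead 108 days is the mean among takers, then at p = 0.30 and c = 0 the overall mean is 32.4 and the SD 49.5. The difference detectable with 80% power (equal SD) is then (1.96 + 0.84) × 49.5 × √(2 × 1.03/57) ≈ 26 days, about 81% of the mean.

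**The case against.** The strongest reply is that the calculation is correct on its inputs and that no figure in the protocol proves them wrong. That stands. A reader might infer that the trial simply does not have 80% power. The bound does not show this, because the loss depends on a 12-month share that the document does not report.

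Four further inferences go too far:

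- **Using 30% as the trial's share.** The Background figure covers first spells over adulthood among employed people with CMD. It is not a one-year rate in employees selected by GHQ-12 or by expecting sick leave. It makes 76% in one year look high, but it cannot stand in for p.
- **Reading the exclusion criterion as a cap on follow-up.** Fewer than 14 CMD days in the past three months limits past leave only. Participants are chosen for raised future risk, and nothing limits their next 12 months.
- **Treating 76% as the threshold for 80% power.** It is the threshold for the two inputs to coexist. If the effect comes entirely from shorter spells and takers do not vary, p = 0.70 already reaches 80%.
- **Taking the true effect to be only a few days.** With 108 days per taker, a 30% reduction is 9.7 days at p = 0.30 (of 32.4) and 16.2 days at p = 0.50 (of 54).

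Nor is the validity of the test in question: Data analysis specifies estimating equations with robust variance. None of this supplies a justification for the mean and SD used.

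**Conclusion.** The point holds in conditional form. The 80% power is arithmetically right but requires at least 76% of control employees to take CMD sick leave within a year, and more than that once leave-takers differ in duration. The protocol does not justify this share. It sits badly with an at-work population screened for little recent CMD leave and with the single proportion the protocol reports.

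Under assumed shares, power for a 30% reduction is about 10–22% at p = 0.30 and 15–45% at p = 0.50. At p = 0.70 it is 63–80% with no variation among takers, and lower with variation. These ranges rest on 57 per arm, a design effect of 1.03, the normal approximation, a duration spread from c = 0 to c = 1, and the three effect mechanisms shown. The 76% bound needs only that days cannot be negative.

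**What to change.** Rewrite the Statistical power paragraph:

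- Replace the unconditional 80% claim with the power, or the detectable difference, of 38 managers and 114 employees over a stated range of zero share, mean and SD. State the assumed mechanism, since it moves the result.
- Take mean, SD and zero share from one source that matches the eligible at-work employees. The protocol already plans to collect sick-leave data for the 24 months before baseline. If such records are used, allow for the fact that the exclusion criteria lower participants' recent leave, so their own pre-baseline figures may understate leave during follow-up.
- State that a non-significant result would not by itself exclude a 30% reduction.

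The cost is one paragraph and a less favourable stated power. Design, enrolment and analysis need not change.

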## Discussion

This paper describes the design of a cluster-randomized controlled trial of a problem-solving intervention for employees at risk of future sick leave due to CMDs. It will be conducted in the workplace, with first-line managers delivering the intervention or a control condition. The primary aim is to evaluate the intervention’s effectiveness to prevent sick leave due to CMDs. The secondary aims are to assess the effects of the intervention on general health, psychological symptoms, work performance and work ability, the psychosocial work environment and the psychosocial safety climate. To the best of the authors’ knowledge, this study is the first to evaluate the problem-solving intervention as a preventive intervention including first-line managers.

The present study employs an intervention starting with training of the first-line managers, and thereafter, the first-line managers use the problem-solving intervention in meetings with their employees who are at risk of future sick leave. Previous studies point to the potential of problem-solving confidence and self-efficacy mediating outcomes such as positive affect, job- and life satisfaction [64], which in turn, are associated with mental health and subjective wellbeing [65, 66]. The problem-solving intervention used in the current study is a short intervention, consisting of 2 to 5 sessions. By means of a thorough, mixed-method process evaluation based on a systematic approached using complementary theoretical frameworks [58, 59], data are collected at employee- and first-line manager levels, and at different timepoints, i.e. before, during and post intervention. The added value of the process evaluation is the link with the findings from the effectiveness evaluation – i.e. to connect the findings of both evaluations. Hence, the process evaluation will enable us to gain in-depth knowledge and insights into the intervention’s mechanisms. It will also make it possible to identify determinants of effective intervention implementation and change mechanisms [67, 68] linked with the effect evaluation.

Previous research indicates that employees with CMDs or mental health symptoms should be given the opportunity to plan and pace their own work [69]. In most cases, support to implement work adjustments from, for example, the first-line manager is needed, because he/she is responsible for leading and allocating the work. In 2015, new provisions about the organizational and social work environment were introduced in Sweden [70]. The new provisions place increased responsibility on the employer to assess physical and psychosocial risks at work and to implement measures to identify, manage and correct potential and real risks. The problem is that first-line management does not always know how to go about this and the provisions do not give guidelines. The problem-solving methodology described in this protocol may be used as a tool for these “corrective measures” with preventive purposes.

The intervention raises ethical issues about personal integrity in relation to employees’ private and working lives and the possible negative consequences of revealing such information to the first-line manager. The employee participating in the current study has the right to choose which matters and/or problems to discuss with the first-line manager and to maintain private life integrity. This is stated in the written information that the employee receives before giving consent to participation. When taking part in the meetings with the first-line manager, the employee is instructed to talk about matters that – from the employee’s perspective - affect his/her work and work tasks. If successful, the problem-solving process may also be applied to the intersection between private life and working life.

### Strengths and limitations

The current study has some important strengths. To start with, a cluster-randomized controlled trial design will be used when evaluating the effectiveness of the problem-solving intervention on the primary outcome, i.e. register-based days of sick leave. The trial will be conducted at several workplaces; these are settings in which there are limited opportunities to conduct a rigorous randomized controlled trial. The cluster-design will allow the first-line managers to provide either the problem-solving intervention or the control condition. The first-line managers in the intervention group will also be told not discuss the intervention with their colleagues outside the intervention group. An additional strength is the use of register data for measuring the primary outcome. The data from the employer’s register and MiDAS will provide objective data about sick leave from day one, and we expect no missing data.

Another strength is the recruitment procedure. We will use a screening procedure to identify employees with early signs of CMD and at risk of future sick leave due to CMDs. Research assistants will screen the incoming answers and administer the baseline measurement to those meeting the inclusion criteria. The assistants have no previous knowledge about the employees and are blinded to group allocation. By using this procedure, we can reduce the risk of selection bias.

We must also mention some limitations. The screening of employees’ risk of future sick leave due to CMDs will be carried out among all employees whose first-line manager participates in the study. There is a potential risk that only employees who have confidence in and a trustful relationship with their first-line manager will respond to the questionnaire, implying that largely motivated employees or employees who only have minor problems will be included in the study. This may affect the generalizability of the study. However, participation is voluntary for both first-line managers and employees. Another limitation is the data collection, with self-reported questionnaires administered at baseline and at 6- and 12-month follow-up, and text messages sent every fourth week during the 12-month follow-up. We cannot rule out the risks of recall bias. However, we suggest that the response burden is appropriate.

### Impact of results

Finding effective ways to prevent or at least reduce the risk of sick leave due to CMDs and using replicable interventions will help employees’ mental health and economic situation and offer benefits in the workplace and in society at large.

There is ample evidence that the psychosocial work environment is vital for the mental well-being of workers, yet many interventions fail to address the psychosocial work environment. Thus, there is a lack of knowledge about workplace interventions which target both the individual employee and organizational change by promoting a good psychosocial work environment. In line with this, the present study will contribute to the area by developing knowledge from a preventive perspective and focusing on employees, first-line managers and their workplaces. This cluster-randomized controlled trial will test the effectiveness of an intervention based on problem-solving principles which aims to prevent the risk of sick leave due to CMDs.

## Data Availability

The current article describes a study protocol, and therefore data sharing is not applicable as no datasets have yet been generated or analyzed.

## Abbreviations

CBT: Cognitive Behavioral Therapy
CFIR: Consolidated Framework for Implementation Research
CMD: Common Mental Disorders
COPSOQ: Copenhagen Psychosocial Questionnaire
GHQ: General Health Questionnaire
LISA: Longitudinal integrated database for health insurance and labor market studies
MiDAS: Micro Data for the Analysis of Social Insurance
PSC: Psychosocial Safety Climate
RTW: Return to Work
OECD: Organisation for Economic Co-operation and Development
s-ED: Self-rated exhaustion Disorder
SSIA: Swedish Social Insurance Agency
